## Abstract

**Background:**

Scar visibility is multifactorial and skin closure technique is thought to play an important role. It is an established principle in plastic surgery that Z plasties generally reduce scar contracture by breaking up the lines of tension in a wound. As an extension of this principle, it is postulated that irregular “deckled” skin incisions made during tumor excision would produce aesthetically superior scars.

**Objective:**

The primary objective of this study is to assess both the clinician and patient opinion of scar quality using the Patient and Observer Scar Assessment Scale (POSAS). Secondary objectives include the proportion of scars judged as good by the both the patient and clinician (less than or equal to 5 on the overall PSOAS scale), the number of adverse events, and the proportion of the scar visible at 1 meter.

**Methods:**

The deckling study will be a patient-blinded, simple randomized controlled trial (RCT) at a single center institution. The two groups will be equally allocated on a 1:1 ratio into the control and treatment arms. All patients greater than 18 years of age undergoing a plastic surgery procedure involving excision of skin lesions will be enrolled. Any patients requiring re-excision through the wound or undergoing injectable corticosteroid therapy will be excluded. A total of 500 patients will be enrolled. The patients will be followed-up at 1 week, 3 months, and 6 months post-operatively.

**Results:**

The study is expected to begin enrolment in August 2016. We anticipate that the deckling study group will have superior scar outcomes when compared to the straight line incision. From clinical experience this is especially true for lesions involving the face and in those areas of the skin that have undergone radiation therapy. The study will be funded by the Plastics and Reconstructive Surgery Department at St Vincent’s Hospital, Sydney, Australia. Ethics approval has been obtained for the study. Conclusion: We believe this will be an important study to assess a novel method to improve the appearance of post-operative scars. The deckling study is simple to master, can be applicable to almost any surgical procedure, and can have good generalizability to a large population cohort.

**Conclusions:**

We believe this will be an important study to assess a novel method to improve the appearance of post-operative scars. The deckling study is simple to master, can be applicable to almost any surgical procedure, and can have good generalizability to a large population cohort.

**Trial Registration:**

Australian New Zealand Clinical Trials Registry (ANZCTR): ACTRN12616000193471; https://www.anzctr.org.au/Trial/Registration/TrialReview.aspx?ACTRN=12616000193471 (Archived by Webcite at http://www.webcitation.org/6gmG8yf1A)

## Introduction

### Disease Background

Scar visibility is multifactorial and skin closure technique is considered to play an important role. It is an established principle in plastic surgery that Z plasties generally reduce scar contracture by breaking up the lines of tension in a wound. As an extension of this principle, it is postulated that irregular “deckled” skin incisions made during tumor excision would produce aesthetically superior scars. A previous unpublished pilot study at St Vincent’s Hospital was conducted to look at deckled incisions versus straight incisions on head and neck lesions in 47 patients. It showed a statistically significant (*P* <.001) smaller detectable scar length ratio with the deckled incision compared to straight line incisions [1]. There are a limited number of studies that describe the use of the deckled incision in literature and they report improved scar formation and reduced contracture rates [2-4].

### Study Rationale

The aim of the study is to assess and quote whether using the deckled incision improves post-operative scars compared to the standard straight line incision. We hypothesize that the deckled incision has superior scar outcomes. Previous studies have been underpowered and had a number of biases as they were not conducted in a randomized fashion. The deckling study will be a patient-blinded, simple randomized controlled trial (RCT) at a single center institution. The two groups will be equally allocated on a 1:1 ratio into the control and treatment arms.

## Methods

### Objectives

The primary objectives of the study are (1) to assess clinician opinion of scar quality using the observer component of the Patient and Observer Scar Assessment Scale (POSAS); and (2) to assess the patient’s opinion of scar quality and/or sensation using the patient component of POSAS.

The secondary objectives are (1) to assess the proportion of scars described as good by the clinician (determined by ≤5 on the overall component of the POSAS); (2) determine the number of adverse events overall and by individual components (namely dehiscence infection, keloids); and (3) calculate the percentage of the scar visible as a percentage of the total length at 1 month.

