### Participants

The study will be solely undertaken at St Vincent’s Public Hospital. The care providers involved with the study will include plastics and reconstructive surgery consultants and registrars. A total of 500 patients will be recruited and divided evenly into the two treatment groups.

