### Statistical Consideration

Sample size was calculated on the basis of a type I error of 5% (ie, *P* <.05) and a type II error of 10% (ie, power of 90%) with the aid of a statistician. Using formal sample size calculations we estimated a sample size of 250 patients for each treatment group. We anticipate an attrition rate of 10%, and subsequently, have increased our sample size by that amount for each treatment group.

Statistical analysis will be carried out by an external statistician. We intend to use independent two-sample *t* tests on primary endpoints and both chi-squared and independent two-sample *t* tests on secondary endpoints.

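### The overall POSAS rating is compared between arms only as a proportion at ≤5; adding a full-scale comparison is cheap and usually more powerful, though the size of the gain depends on inputs the article does not give

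*Protocol article*

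**What the plan says.** In the protocol article, the Objectives section names two primary objectives: the observer component and the patient component of the POSAS, with no cut-point on either. The overall rating enters through the first secondary objective: "to assess the proportion of scars described as good by the clinician (determined by ≤5 on the overall component of the POSAS". The abstract gives the same threshold but a different rater: "the proportion of scars judged as good by the both the patient and clinician (less than or equal to 5 on the overall PSOAS scale".

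Under Statistical Consideration, one sentence sets the tests: "We intend to use independent two-sample *t* tests on primary endpoints and both chi-squared and independent two-sample *t* tests on secondary endpoints". It does not say which secondary endpoint gets which test.

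The same section gives the error rates ("Sample size was calculated on the basis of a type I error of 5"% and "a type II error of 10% (ie, power of 90"%) and the size ("Using formal sample size calculations we estimated a sample size of 250 patients for each treatment group"). It ties the 90% power to no endpoint, and it states no effect size, standard deviation or expected proportion of good scars. The POSAS is scheduled at 1 week, 3 months and 6 months (Table 1), so the graded rating will be in hand.

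**The concern.** The overall rating is a graded global judgement, and the study's hypothesis is a graded one: better-looking scars. Cutting at ≤5 discards every difference within the good range and every difference above it. A scar that moves from 4 to 2, or from 9 to 6, counts as unchanged. The article gives no reason to expect the benefit to concentrate at the step from 5 to 6.

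At stake is the readability of the secondary evidence. With the cut as the only listed comparison of this rating, a real shift could give a non-significant result where a full-scale comparison would have detected it. A reader might then wonder why the global rating does not agree with the component scores. The trial's primary conclusion is not at stake.

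**Working it through.** **1. The plan's own figure.** The 250 per group cannot be reproduced, because no effect size, variability or endpoint is given. It can only be solved backwards.

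**2. Inputs**
- From the article: type I error 5%, power 90%, 250 per group, anticipated attrition 10%.
- Derived: 250 × 0.9 = 225 evaluable per group. Both 225 and 250 are used, because the text leaves unclear whether 250 is before or after the attrition allowance.
- Assumed: two-sided test, one independent rating per patient, a normally distributed rating shifted by the same amount throughout, and control proportions good of 10% to 90%.

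**3. Shift that gives a full-scale test 90% power.** d = (1.960 + 1.282) × √(2/n).
- n = 225: d = 3.2415 × 0.0943 = 0.306
- n = 250: d = 3.2415 × 0.0894 = 0.290

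**4. The same shift after the cut.** If a proportion p0 of control scars is good, the treated proportion is p1 = Φ(Φ⁻¹(p0) + d). With p̄ = (p0 + p1)/2,

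power = Φ( [√n (p1 − p0) − 1.960 √(2p̄(1−p̄))] / √(p0(1−p0) + p1(1−p1)) ).

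Example with n = 225 and p0 = 0.80: p1 = Φ(0.842 + 0.306) = 0.874. Power = Φ((1.115 − 1.023)/0.520) = Φ(0.177) = 57.0%.

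| Control good | Treated good | Power after cut | Loss from 90% (points) |
|---|---|---|---|
| 10% | 16.5% | 52.4% | 37.6 |
| 20% | 29.6% | 65.5% | 24.5 |
| 30% | 41.3% | 71.1% | 18.9 |
| 40% | 52.1% | 73.1% | 16.9 |
| 50% | 62.0% | 72.9% | 17.1 |
| 60% | 71.2% | 70.6% | 19.4 |
| 70% | 79.7% | 65.8% | 24.2 |
| 80% | 87.4% | 57.0% | 33.0 |
| 90% | 94.4% | 40.9% | 49.1 |

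At 250 per group the losses agree within about 0.3 points.

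**5. Without the 90% anchor.** With 225 per group and 50% of control scars good:

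| d | Full-scale power | Loss (points) |
|---|---|---|
| 0.10 | 18.4% | 5 |
| 0.15 | 35.6% | 11 |
| 0.20 | 56.4% | 17 |
| 0.25 | 75.5% | 20 |
| 0.30 | 88.9% | 18 |
| 0.35 | 96.0% | 12 |
| 0.40 | 98.9% | 7 |
| 0.50 | about 100% | 1 |
| 0.60 | about 100% | about 0 |

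Over all the shifts and control proportions tried, the loss ran from 0.1 to 49 points.

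**6. Discrete check by simulation.** The rating was assumed to run from 1 to 10, with SD 2, mean shift 0.61 and 225 per group. The t test had 87% to 90% power and the uncorrected chi-squared test 42% to 74%, depending on the control mean.

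**7. A case that reverses the order.** Start from 50% good in control. Move half of the 6s and 30% of the 7s to 5 and change nothing else, so that 64% are good under treatment. The t test then had about 18% power and the chi-squared test about 86%.

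**The case against.** The strongest reply is that the main POSAS analysis is not dichotomised at all. Clinician and patient opinion are compared on their own scales by t tests as primary endpoints, and a responder proportion beside a full-scale primary is a common and legitimate complement. That stands. It limits the point to one secondary item and means the proportion should be kept.

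Second, a reader might infer that the cut costs at least 15 points of power whatever the truth. The documents do not support that. They give none of the inputs, the 90% power is attached to no endpoint, and the tables above show losses near zero for large effects and about 5 points for a small one. The order can even reverse.

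Third, the article does not assign tests to secondary endpoints, nor say whether the overall rating also enters the component scores; the scale forms are in appendices that are not reproduced. Chi-squared for the proportion is therefore an inference, though the natural one, and it cannot be shown that the rating is never used uncut.

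Fourth, a reason for ≤5 may stand in the full protocol, which the article condenses. Its absence from the article is accordingly not the point. What remains is the stated choice: the only listed endpoint built on the overall rating is the proportion.

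**Conclusion.** The point holds as a low-severity improvement. If a full-scale comparison of the overall rating had 90% power under a uniform normal shift, the ≤5 proportion would have at most about 73%. It would have about 57% if 80% of control scars are good and 41% if 90% are. These figures rest on a two-sided 5% test, 225 to 250 independent ratings per group, and an assumed shift and distribution that the article does not state. Outside those conditions the loss may be small, and an effect located mainly at the cut would favour the proportion. It would be wrong to read this as a loss of power for the primary endpoints, or as a shortfall against power promised for this secondary endpoint; the article promises none.

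**What to change.** Add the between-arm difference in the overall POSAS rating on its full scale as a secondary comparison, and make it the main test of that item. Use the two-sample t test already planned, or a rank or ordinal equivalent. Report the ≤5 proportion with its confidence interval alongside as the responder summary. In the same edit, reconcile the abstract (patient and clinician) with the Objectives section (clinician only) on whose rating defines a good scar.

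The cost is about one sentence in the objectives and statistics sections, with no new data, visits or patients. The downsides are one more secondary comparison and a mean or ordinal difference that is less immediate to read than a percentage.

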### Design

The deckling study will be a patient-blinded, simple RCT at a single center institution. The two groups will be equally allocated on a 1:1 ratio into the control and treatment arms. There will be two groups: those that receive the deckled incision and those that receive the standard straight line incision.

### Participants

The study will be solely undertaken at St Vincent’s Public Hospital. The care providers involved with the study will include plastics and reconstructive surgery consultants and registrars. A total of 500 patients will be recruited and divided evenly into the two treatment groups.

### Duration

The study will be conducted over a period of 24 months with ongoing recruitment or until the total sample size required is reached.

### Inclusion and Exclusion Criteria

Inclusion criteria for the study include (1) greater than or equal to 18 years of age; (2) able to give informed consent and willingness to participate in follow-up; and (3) undergoing any plastic surgery procedure involving excision of skin lesions. Exclusion criteria include those requiring re-excision through the original wound and undergoing injectable corticosteroid therapy into the scar.

The patients will be randomly allocated to receive either the deckled incision or the straight line incision for their surgery. In patients with multiple (two or more) separate lesions requiring separate incisions, each lesion will be randomly allocated to receive either the deckled or straight line incision. Only the treating surgeon will be aware of which incision was used and the patient will be blinded to the type of incision. The surgeon will document in the operation note the number and site of lesions, whether they were deckled or not, the precise length of the scar, and whether the procedure was carried out by a registrar or consultant.

The patient will be followed-up in the outpatient clinic. Standard post-operative care with micropore tape will be given to both groups with respect to scar minimization. The scar and compliance with standard post-operative scar reduction will be assessed at 1 week, 3 months, and 6 months post-operatively using the POSAS [5]. The 6-month cut off was chosen as scars have usually matured by 6 months to reflect their final life-long appearance and to avoid a large number of patient attrition over a longer follow-up period (Figure 1).

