### Investigation Plan

The intervention plan is shown in Table 1.

**Table 1 table1:** Intervention plan.

List interventions	Enrolment visit	1 Week	3 Months	6 Months
Informed consent	✓			
Inclusion/exclusion criteria	✓			
Medical history	✓			
Patient and observer scar assessment scale (POSAS)		✓	✓	✓
Adverse event and serious adverse event assessment		✓	✓	✓

The follow-up will be done in the outpatient setting. The POSAS requires at least three independent assessors to achieve a valid result and this will be done by a combination of medical and nursing staff. The results will be recorded in real-time on a tablet (iPAD), which has been pre-populated with the patient demographics and the unique study code identifier that can be cross referenced with the medical records. The data is automatically backed up to an online database via Dropbox. Selected photographs will be taken by a digital camera for future publication purposes.

The routine standard of follow-up will vary with each individual procedure and thus the above protocol is not the standard of care. The additional costs of the procedure will be covered by the Plastics and Reconstructive Surgery Department.

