### Enrolment Procedure

The participant will be enrolled into the study after the informed consent process has been completed, and the participant has met all inclusion criteria and none of the exclusion criteria. The patient’s baseline characteristics will be recorded on a pre-populated A4 sheet and scanned via email to a single email address. The patient baseline characteristics that will be recorded are age, gender, smoking, Fitzpatrick classification of skin type and ethnicity, presence of vascular co-morbidities, diabetes, use of systemic and/or oral steroids or immunosuppressant’s, previous poor scar results, site of lesions (face vs trunk vs limbs), and previous radiotherapy over the surgical site. An independent person will subsequently enter the patient data into an online database and allocate a study code, which will be documented in the patient records.

The final statistical analysis will be stratified and adjusted by the patients’ baseline characteristics to adjust for their effects on wound healing. We are particularly interested in effects of previous radiotherapy and sites of lesions (face vs trunk vs limbs) as we believe that the deckling incision will offer the most benefit in those with previous radiotherapy and in lesions on the face.

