### Randomization Procedure

Following suitability for enrolment into the study and allocation of study code, the participants will be randomized to receive either the deckled incision or the standard straight line incision in a simple fashion using a random computer number generator. This will be done in the anesthetic bay after confirmation of patient suitability by checking the medical records. The surgeon will subsequently ring an external number and the study nurse will specify what treatment the individual lesions will receive.

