### Blinding

In order to achieve allocation concealment an external third party will be used to assign the treatment group. The surgeon will document in the patient notes which incision was carried out for a specific lesion. This will be entered into the patient database by an independent third party.

The patient will be blinded to the type of incision that is done for any given lesion. However, it is impractical to blind the individual surgeon. In addition, the outcome adjudicators will also be blinded to the incision used. The data collectors and analysis will be centralized and remain independent of the outcome adjudicators at all times. Medical record numbers will also be recorded to enable tracking of progress over time.

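### Steroid injection into the scar and re-excision through the wound are listed as exclusions, but neither study scar nor study wound exists when eligibility is checked, so the criteria can act after randomisation and, for steroid, on the outcome itself

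*Protocol article*

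**What the plan says.** The exclusions appear twice in the protocol article. Under Inclusion and Exclusion Criteria: "Exclusion criteria include those requiring re-excision through the original wound and undergoing injectable corticosteroid therapy into the scar". In the abstract's Methods: "Any patients requiring re-excision through the wound or undergoing injectable corticosteroid therapy will be excluded". The body joins the two conditions with *and*, the abstract with *or*; I read both as two separate criteria. Neither gives a time point.

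Three other places fix when eligibility is judged:

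- Enrolment Procedure: a participant enters once "the participant has met all inclusion criteria and none of the exclusion criteria".
- Investigation Plan, Table 1: the row "Inclusion/exclusion criteria" is ticked at the enrolment visit and at no later visit.
- Randomization Procedure, on the randomisation itself: "This will be done in the anesthetic bay after confirmation of patient suitability by checking the medical records".

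The scar is "assessed at 1 week, 3 months, and 6 months post-operatively using the POSAS". Both primary objectives are POSAS scores, observer and patient. A secondary objective is to "determine the number of adverse events overall and by individual components (namely dehiscence infection, keloids"). The Blinding section says that the surgeon cannot practically be blinded, while patients and outcome adjudicators are.

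**The concern.** An exclusion criterion should be a fact that is settled before allocation. Randomisation takes place in the anaesthetic bay, before the incision. If the scar and the wound in the criteria are those made by the study surgery, nobody can meet either criterion at the eligibility check, and the criteria can act only by removing patients who have already been randomised.

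For steroid injection the difficulty goes further. Injecting a scar is ordinarily a response to a poor scar, and scar quality is the primary outcome. Removing injected scars would select the analysed group on the quantity being compared. Keloids among those scars could also leave the secondary endpoint that counts them. A treating surgeon who knows the incision could, without any intent to bias, reach the decision to inject at different rates in the two arms.

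Re-excision after the study surgery would likewise be an exclusion after randomisation, which the allocated incision could influence. The article gives no reason for re-excision, so no link with scar quality is shown.

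**Working it through.** **Reading the text.** Elsewhere in the section that lists the criteria, the scar means the study scar: its length goes into the operation note, and it is scored at three follow-up visits. Two readings of the steroid criterion are open.

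1. *Study scar.* The criterion cannot be met at enrolment or in the anaesthetic bay. It then either does nothing or removes patients after randomisation.
2. *A scar from before the trial.* The criterion fits the enrolment check, but the text does not say this and uses the word in another sense in the same section.

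For re-excision the second reading is easier: a patient may be referred with a lesion that was incompletely excised elsewhere.

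**Size: inputs.** The article gives no effect size, SD or exclusion rate, so its 250 per group cannot be reproduced. The figures below are an illustration.

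- From Statistical Consideration: type I error 5% (sidedness not stated; two-sided assumed), power 90%, 250 per group, attrition 10%, independent two-sample *t* test.
- Back-solved true difference: d = (1.960 + 1.282) × √(2/250) = 0.290 SD (0.262 if one-sided).
- Evaluable per arm: 250 × 0.90 = 225. With nobody excluded, power at 0.29 SD is Φ(0.29/√(2/225) − 1.96) = 86.8%.
- Assumed: 2%, 5% or 10% of control scars excluded (q); correlation ρ between the severity that triggers exclusion and POSAS of 0.5, 0.7 or 1.0.

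**Model.** Scores are N(0, 1) in control and N(−d, 1) in the deckled arm, lower being better. A scar is excluded when a latent severity with unit variance and mean ρμ (μ the arm mean) exceeds c = z(1−q). With a = c − ρμ and λ = φ(a)/Φ(a), the retained mean is μ − ρλ and the retained variance is 1 − ρ²(aλ + λ²).

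**Worked case, ρ = 0.7, q = 5%.**

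- Control: a = 1.645, λ = 0.109, mean = −0.7 × 0.109 = −0.076.
- Deckled: a = 1.645 + 0.7 × 0.29 = 1.848, λ = 0.075, mean = −0.29 − 0.7 × 0.075 = −0.342; 3.2% excluded.
- Retained difference: 0.342 − 0.076 = 0.266 SD, an attenuation of 8.2%.

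**All cases.**

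| ρ | Control excluded | Deckled excluded | Difference (SD) | Attenuation | Power |
|---|---|---|---|---|---|
| 0.5 | 2% | 1.4% | 0.283 | 2.3% | 85.4% |
| 0.5 | 5% | 3.7% | 0.277 | 4.3% | 83.7% |
| 0.5 | 10% | 7.7% | 0.271 | 6.7% | 81.0% |
| 0.7 | 2% | 1.2% | 0.278 | 4.3% | 84.7% |
| 0.7 | 5% | 3.2% | 0.266 | 8.2% | 82.3% |
| 0.7 | 10% | 6.9% | 0.253 | 12.7% | 78.5% |
| 1.0 | 2% | 1.0% | 0.266 | 8.1% | 83.4% |
| 1.0 | 5% | 2.7% | 0.244 | 15.7% | 79.2% |
| 1.0 | 10% | 5.8% | 0.218 | 24.8% | 72.7% |

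The attenuation does not depend on the number evaluable. With all 250 per arm evaluable and ρ = 1.0, power falls from 90% to 83% (q = 5%) and 77% (q = 10%).

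**Unequal exclusion with no true effect.** If the worst scars are removed at different rates q₀ and q₁, the spurious difference is ρ × [λ(q₁) − λ(q₀)], where λ(q) = φ(z(1−q))/(1−q). The values are λ(2%) = 0.049, λ(5%) = 0.109 and λ(10%) = 0.195.

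- 2% against 5%: 0.03 SD (ρ = 0.5) to 0.06 SD (ρ = 1.0).
- 5% against 10%: 0.04 SD to 0.09 SD.

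With standard error √(2/225) = 0.094, the two-sided type I error rises from 5% to between about 6% and 15%. The sign depends on which arm loses more scars.

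**The case against.** The strongest reply is that the timing is inferred. No sentence says that a randomised patient is withdrawn or left out of the analysis, and all three procedural places put the check before allocation. On that view the criteria are ordinary eligibility facts, loosely worded. This stands in part: the documents do not show that the trial will discard outcomes. It does not clear the text, because the steroid criterion, read as the section itself uses the word, cannot operate at that check.

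A reader might infer several stronger things that the documents do not support:

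- *That re-excision also removes the worst scars.* No reason for re-excision is given. After tumour excision it may follow from margins.
- *That the analysis is by incision performed.* The Blinding section says "The surgeon will document in the patient notes which incision was carried out for a specific lesion", and that this is entered in the database. It does not say that the allocation given by telephone is not kept, or that analysis follows the incision performed. Analysis sets may be defined in a plan that is not shown.
- *That treated keloids are lost from the safety count.* Adverse events are assessed at every follow-up visit, and nothing says that data from excluded patients are dropped. The loss is possible, not stated.
- *That dilution of 16% to 25% is to be expected.* Those figures (5% and 10% excluded) need exclusion to follow POSAS perfectly, and the exclusion rates have no source in the article.

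**Conclusion.** The point holds as a conflict in the eligibility text. The two statements of the exclusions do not fit the three places that put the check before randomisation. For steroid injection, the natural reading is an exclusion after randomisation that depends on the primary outcome. For re-excision, it is an exclusion after randomisation only if the study wound is meant, and dependence on scar quality is not shown.

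The direction of bias is open. Exclusion by severity alone dilutes a true difference, by about 2% to 25% over the assumed ranges. Unequal exclusion between arms can bias either way; with no true effect it could produce a difference of 0.03 to 0.09 SD. All of this rests on assumed exclusion rates and correlations, normal scores, and a difference of 0.29 SD inferred from the sample size. If the criteria were meant only for the patient's state before randomisation, and are applied so, the bias does not arise and the defect is one of wording.

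**What to change.** 1. Reconcile the abstract and the criteria section with Enrolment Procedure, Table 1 and Randomization Procedure, so that each exclusion names a fact known before the randomisation call. If a wound or scar from before the trial was meant, say so.
2. State that every randomised lesion stays in the primary analysis in its allocated arm.
3. Record later steroid injection and re-excision by arm as post-randomisation events, and add a sensitivity analysis for the affected lesions.
4. Count keloids by arm whether or not they are treated.

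The cost is a change of wording and the recording of two events. The drawback is that scores after an injection reflect the incision together with later care, which the sensitivity analysis should make visible.

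### Simple randomisation of each lesion leaves an expected half of two-lesion patients without a within-patient comparison, and the planned t tests would not use that comparison in the rest

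*Protocol article*

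**What the plan says.** The Inclusion and Exclusion Criteria section first describes allocation by patient: "The patients will be randomly allocated to receive either the deckled incision or the straight line incision for their surgery". For patients with two or more separate lesions it then moves to the lesion: "each lesion will be randomly allocated to receive either the deckled or straight line incision".

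The Randomization Procedure section says that randomisation is done "in a simple fashion using a random computer number generator", after consent, the eligibility check and issue of the study code. It continues: "The surgeon will subsequently ring an external number and the study nurse will specify what treatment the individual lesions will receive". The Design section gives the ratio: "The two groups will be equally allocated on a 1:1 ratio into the control and treatment arms". None of these sections describes pairing, blocking or any other constraint within a patient.

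For the analysis, the Statistical Consideration section says "We intend to use independent two-sample" t tests on the primary endpoints. The Enrolment Procedure section adds that the final analysis will be stratified and adjusted by baseline characteristics. Those include smoking, skin type, diabetes, steroid use, earlier poor scars, lesion site and earlier radiotherapy at the site. It singles out site and radiotherapy as likely to change the benefit.

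**The concern.** Two lesions on one patient share that patient's skin type, smoking, diabetes, medication and unmeasured tendency to scar. If one lesion is deckled and the other straight, the difference between them is free of all of these. The protocol already accepts both incisions in one patient, but it obtains the comparison only by chance. A patient whose lesions all fall in one arm contributes only to the comparison between patients, and no later modelling can restore the missing contrast.

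The analysis has a related gap. Applied to lesions, an unpaired t test ignores which lesions belong to the same patient, so it would leave the contrast unused even in patients who carry both incisions. What is at stake is precision, not validity.

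**Working it through.** **Inputs from the article.** Each lesion is allocated at random; the method is simple; the ratio is 1:1, so the probability is 0.5 per lesion; the primary test is an unpaired t test; the total is 500 patients. The article gives no figure of its own on this point. Its sample size of 250 per group does not bear on it.

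**Assumed inputs, not in the article.** The share *p* of patients with two lesions (5% to 30%, all others having one), and the correlation *ρ* between two lesions of one patient (0.1 to 0.5 for the trial-level figures).

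**Step 1: how often all lesions get the same incision.** For *k* lesions the probability is 2 × 0.5^*k*:
- two lesions: 2 × 0.25 = 0.50 (simulation 0.501)
- three lesions: 2 × 0.125 = 0.25
- four lesions: 2 × 0.0625 = 0.125

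Of 100 two-lesion patients, 50 are expected to have the same incision twice (95% range 40 to 60).

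**Step 2: information per patient on the incision effect.** With lesion variance 1 and arms coded ±1/2:
- single lesion: 0.25
- pair with different incisions: 1 / (2(1 − ρ))
- pair with the same incision: 1 / (2(1 + ρ))

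Simple allocation averages the two pair types, which gives 1 / (2(1 − ρ²)). Forced splitting always gives 1 / (2(1 − ρ)). Among two-lesion patients the ratio is 1 + ρ, that is 1.3 at ρ = 0.3 and 1.5 at ρ = 0.5. At ρ = 0 there is no gain.

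**Step 3: the whole trial.** The information per patient is (1 − p) × 0.25 + p × (pair value). Both columns assume a patient-effect model.

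| p | ρ | Simple | Split | Gain |
|---|---|---|---|---|
| 5% | 0.1 | 0.2375 + 0.0253 = 0.2628 | 0.2375 + 0.0278 = 0.2653 | 1.0% |
| 10% | 0.1 | 0.225 + 0.0505 = 0.2755 | 0.225 + 0.0556 = 0.2806 | 1.8% |
| 10% | 0.3 | 0.225 + 0.0549 = 0.2799 | 0.225 + 0.0714 = 0.2964 | 5.9% |
| 10% | 0.5 | 0.225 + 0.0667 = 0.2917 | 0.225 + 0.1000 = 0.3250 | 11.4% |
| 20% | 0.3 | 0.200 + 0.1099 = 0.3099 | 0.200 + 0.1429 = 0.3429 | 10.6% |
| 20% | 0.5 | 0.200 + 0.1333 = 0.3333 | 0.200 + 0.2000 = 0.4000 | 20.0% |
| 30% | 0.3 | 0.175 + 0.1648 = 0.3398 | 0.175 + 0.2143 = 0.3893 | 14.6% |
| 30% | 0.5 | 0.175 + 0.2000 = 0.3750 | 0.175 + 0.3000 = 0.4750 | 26.7% |

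**Step 4: the planned t test.** For *m* two-lesion patients under simple allocation, the unpaired difference in means has variance 2/*m* at any ρ. Simulation at ρ = 0.5 with 200 patients gave 2.01/*m*. A patient-effect model would bring this to 2(1 − ρ²)/*m*, which is 1.5/*m* at ρ = 0.5. Split allocation would bring it to 2(1 − ρ)/*m*, which is 1.0/*m* (simulation 1.01/*m*). The t test thus gives up precision even under the present allocation. If it were kept after a change to splitting, it would still assume about 2/*m* and so would not deliver the gain.

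**The case against.** The strongest reply is that nothing here is invalid. Random allocation of each lesion is unbiased, and the preference for splitting is one of efficiency. That stands.

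A reader might infer that the within-patient comparison is lost altogether. It is not: on average half of two-lesion patients, 75% of those with three lesions and 87.5% of those with four still carry both incisions. A reader might also infer that the t test gives a false error rate because it ignores clustering. Step 4 does not support that for simple allocation by lesion, where the unpaired variance is about what the test assumes.

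The gain may be very small. The planned baseline adjustment already removes part of what two lesions share, so the correlation that matters is the one left after adjustment. Pairing also does not control lesion site or radiotherapy at the site, which can differ between two lesions of one patient. This is why the range must include low correlations.

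Blinding is a real cost. The Blinding section keeps patients and outcome adjudicators unaware of the incision, and the patient-rated scale is a primary objective. Under simple allocation, recognising one scar says nothing about the other; under a one-of-each rule it reveals the other. About half of two-lesion patients already carry both scar types, so the exposure grows rather than begins.

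Predictability is a weaker objection. Consent and eligibility come before the call, and on the natural reading one call settles all lesions. If the lesions are listed first, no allocation can be foreseen. The article does not expressly state either the single call or independence between lesions; both follow from the plain reading of its text. The full protocol, not shown, could contain a constraint that the article omits.

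**Conclusion.** The point holds as a low-priority improvement in design and analysis. As described, an expected half of two-lesion patients and a quarter of three-lesion patients give no within-patient comparison, and the stated t tests would not use it in the others. The allocation is valid and unbiased.

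The size cannot be fixed from the article. It is about 1-2% more information at 5-10% two-lesion patients and ρ = 0.1, and 6-27% at 10-30% and ρ = 0.3-0.5, falling to nothing at ρ = 0. On 500 patients that corresponds to between 500 × 0.01 = 5 and 500 × 0.267 ≈ 133 further patients under the present rule. These figures model patients with one or two lesions only, and they assume a patient-effect model under both allocations. Changing the allocation while keeping the t test would not achieve them.

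**What to change.** In the Inclusion and Exclusion Criteria and Randomization Procedure sections, state that for patients with two or more lesions the surgeon lists the lesions in a fixed order before the call. The study nurse then allocates them in pairs, one deckled and one straight, with the order within each pair drawn at random. An odd last lesion is allocated at random.

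In Statistical Consideration, replace the t tests by a model with a random patient effect and the baseline adjustment already promised under Enrolment Procedure. Lesion site and previous radiotherapy should enter at lesion level. The allocation and the analysis should change together.

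The cost is a second allocation list and a fixed lesion order, with no extra patients. The allocation can be changed only for patients not yet randomised, and the article describes enrolment as still to begin; the model is worth adopting even if the allocation stays as it is. The downside to weigh is that every multi-lesion patient, instead of about half of those with two lesions, will carry both scar types, and that recognising one scar of a pair reveals the other to patient and assessor.
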